#### Learning phase

Participants will have to match each of the 12 target pictures in the pile (lefthand side of screen) with an identical one hidden in the grid. In order to encourage them to explore the whole grid and avoid making the test too simple, for each trial, four boxes will be blocked: the box identified in the previous trial, and three others at random. When a pair is found, the relevant picture on the lefthand side of the screen will be marked with a green tick, and the participant will no longer be able to click on it. The learning phase will end when all the pairs have been constructed. To make the social memory task appear more like a game, participants will have to match each pair before the cursor on the righthand side of the screen is lowered. To avoid setting participants up for failure, the cursor will only be lowered after a pair is found, and not after each trial.

#### Recall phase

The recall phase will take place after an interference task (completion of a questionnaire), and will consist of picture recognition and grid location recall. For the picture recognition, all 24 pictures (i.e., 12 targets and 12 distractors) will be displayed one by one in random order. For each picture, participants will have to say whether or not they saw the picture in the learning phase. For the location recall, the 12 target pictures will be displayed one by one, and participants will have to place each one in the box it occupied in the learning phase.

#### Procedure for social memory task

The learning phase will take place in three social contexts: (1) *presence-only* context, where the participant performs the task alone, with the dyadic partner present in the same room but behind a screen; (2) *observation* context, where the participant observes the dyadic partner performing the task; and (3) *collaboration* context, where the participant and the dyadic partner perform the task together. Each dyad will perform the task in all three contexts. The order of the three contexts will be randomly counterbalanced across the dyads.

During the learning phase, regardless of the context (presence-only, observation, or collaboration), the participant, dyadic partner, and experimenter will all be present in the room (see Fig. 2 for room layout). The tables of the two members of the dyad will be placed side by side facing a wall, and the experimenter’s desk will be perpendicular to these two tables, more than 1 m away. In the presence-only context, the touchscreen will be placed between the participant’s table and the dyadic partner’s table. The dyadic partner will complete a questionnaire during this learning phase. In the observation and collaboration contexts, the dyadic members’ tables will be fixed together, and the touchscreen will be placed in the middle.

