#### Demographic data

The relationship with the dyadic partner will be documented: nature of relationship (relative, friend, other), feeling of closeness, and number of years they have known each other. Some demographic information will also be collected: age, sex, highest degree obtained, living alone or not.

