### MEM&SO study procedure

MEM&SO is a comparative cross-sectional study. Participants will be recruited from several centres (Caen, Rennes, Rouen, and memory clinics in Normandy). HC will be recruited in and around Caen, and the examinations of all participants will be performed in Caen. Registered on ClinicalTrials.gov (no. NCT05800028).

After the inclusion phase, the study will take place over 3 half-days, corresponding to the three study visits (see Fig. 3). Each visit will last 90 min, with a 10-minute break in the middle.

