### Data analysis plan

Each participant’s performance in the presence-only context will serve as a reference score, and a differential score will be calculated by subtracting this reference score from the participant’s memory performance in the collaboration context. The *z* score of this differential score will then be calculated, based on the mean and standard deviation for the HC group. This will show whether each patient’s differential score differs significantly from that of the HC group. The same analyses will then be carried out for performance in the observation context.

As this study is designed to identify determinants (social interactions and abilities, cognitive skills, and personality traits) that could explain the differential scores for the collaboration and observation contexts, we will carry out multiple comparative case analyses [48–50], based on the differential scores for the collaboration context of at least three patients whose memory performance is substantially better in the collaboration condition, compared with the presence only condition, and for three patients whose performance is only minimally better. These six patients will be compared on their social skills (social interactions and abilities), personality (especially the cooperation and determination dimensions), and memory performance in classic neuropsychological tests. Following a logic of replication, other patients will be added to the analyses, to see whether a regular pattern emerges. The same analyses will be conducted on differential scores for the observation context.

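### Counterbalancing removes order effects from group averages only, but the analysis scores and selects single patients without accounting for the order each one had

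*Protocol article*

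**What the plan says.** Under Procedure for social memory task, the protocol article states "Each dyad will perform the task in all three contexts" and "The order of the three contexts will be randomly counterbalanced across the dyads". The caption of Fig. 3 repeats the counterbalancing note. Under MEM&SO study procedure, "the study will take place over 3 half-days, corresponding to the three study visits".

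The Data analysis plan then fixes three steps.

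- **Differential.** The presence-only score is the reference: "a differential score will be calculated by subtracting this reference score from the participant"'s collaboration score. The same is done for observation.
- **Standardisation.** A z score is computed "based on the mean and standard deviation for the HC group". It is meant to show whether each patient's "differential score differs significantly from that of the HC group".
- **Case selection.** The comparison starts from "at least three patients whose memory performance is substantially better in the collaboration condition" relative to presence-only, set against three patients who gain little. These cases are compared on social skills, personality and memory tests, and further patients are then added to see whether the pattern repeats.

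Order appears in none of these steps.

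**The concern.** Counterbalancing protects a contrast of averages, because orders that favour collaboration offset orders that work against it. It does nothing for one patient, who has a single order in which context and position are fully confounded. The planned z score and the choice of cases both operate at that level.

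An order effect is plausible. The same 12-box grid game is played three times with only the pictures changed, and after the first recall session the participant knows what will be tested.

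At stake is the secondary objective. If patients reach the high-gain or low-gain set partly because of their order, the study may look for social, cognitive or personality reasons for what is partly a scheduling effect. Order is not among the characteristics on which the cases are to be compared.

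**Working it through.** The plan states no order effect and no SD for the differential, so there is no figure to reproduce. The check asks how much order would matter over a range of assumed effects.

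**Inputs from the article.** Three contexts, hence 6 possible orders; 30 AD, 16 svPPA and 46 HC dyads; z on the overall HC mean and SD; at least three high-gain and three low-gain cases.

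**Assumptions.** One context per visit (inferred, as Fig. 3 is not shown). A linear order effect λ per visit, in units of the residual SD of the differential, with λ = 0, 0.1, 0.25 or 0.5. The same λ in patients and HC unless stated otherwise. No true difference between patients.

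**Step 1: lag.** Let k be the position of collaboration minus the position of presence-only (P presence-only, O observation, C collaboration).

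| Order | POC | PCO | OPC | OCP | CPO | COP |
|---|---|---|---|---|---|---|
| k | +2 | +1 | +1 | −1 | −1 | −2 |

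The mean is 0 and the variance is (4+1+1+1+1+4)/6 = 2. The zero mean is why a balanced group average is safe. No single patient has k = 0.

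**Step 2: z score.** With D = context effect + λk + e and SD(e) = 1, the HC SD is s = √(1 + 2λ²). A patient's z shifts by kλ/s. The chance of exceeding +1.96 with no true difference is 1 − Φ(1.96s − kλ). Example: λ = 0.25 gives s = √1.125 = 1.061; for k = +2 the shift is 0.5/1.061 = 0.47 and the tail is 1 − Φ(2.079 − 0.5) = 5.7%.

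| λ | s | z shift at k = ±2 | Upper tail, k = +2 | Upper tail, k = −2 | Two-sided rate averaged over orders |
|---|---|---|---|---|---|
| 0 | 1.000 | 0 | 2.5% | 2.5% | 5.0% |
| 0.1 | 1.010 | ±0.20 | 3.8% | 1.5% | 5.0% |
| 0.25 | 1.061 | ±0.47 | 5.7% | 0.5% | 5.0% |
| 0.5 | 1.225 | ±0.82 | 8.1% | 0.03% | 4.7% |

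The average stays near 5% because HC have varied orders too, so order variance is inside the HC SD: 2λ²/(1 + 2λ²) = 2%, 11% and 33% of the variance. The price is sensitivity. A true shift of one residual SD is scored as 1/s = 0.99, 0.94 or 0.82.

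**Step 3: case selection.** Simulation of 30 AD patients, 5 per order, taking the three highest and three lowest differentials:

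| λ | Highest three: collaboration after presence-only | Lowest three: same |
|---|---|---|
| 0 | 50% | 50% |
| 0.1 | about 61% | 39% |
| 0.25 | 77% | 24% |
| 0.5 | 93% | 8% |

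**Step 4: candidate corrections.** If HC gain 0.25 SD per visit and patients gain nothing, subtracting the HC slope from the patients drives the share in the highest three down to 24%, a bias in the other direction. Subtracting the order effect estimated in the patients' own group returns it to 50% in every scenario tested.

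**The case against.** **The size is assumed.** This stands. The documents give no order effect. The picture sets differ between contexts, practice and fatigue push in opposite directions, and a practice gain across visits cannot be presumed in amnesic AD. At 0.1 SD per visit the effect is small.

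**Order is allocated at random, so it is unrelated in expectation to personality or social skill.** Largely right. Order mainly adds noise that blurs the determinants. But the comparison starts from about six patients, where chance alignment is easily taken for a pattern, and adding patients chosen on the same score does not remove the problem.

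**The plan does not literally take the top and bottom three.** Also right. The simulated highest and lowest three stand in for the planned high-gain and low-gain cases.

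Three stronger readings are tempting but not supported.

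- *The z scores produce too many false positives overall.* They do not, because HC are counterbalanced as well.
- *Age, sex and education feed directly into z.* The article records them ("Some demographic information will also be collected: age, sex, highest degree obtained"), but any effect that is equal across contexts cancels when a person's own presence-only score is subtracted. Only an interaction with context would remain, and the documents give no evidence of one. That matching is not described proves nothing in a condensed article.
- *Orders are unbalanced within the diagnostic groups.* Counterbalancing across dyads does not exclude doing so within groups. All that can be said is that 16 and 46 are not multiples of 6, so six orders cannot be exactly equally frequent in svPPA or HC.

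**Conclusion.** The concern holds for order and not beyond it. The design handles order at the level of the average, while the stated analysis infers and selects at the level of the patient. The method is fixed in the Data analysis plan, so this is not a detail left to another document. If an order effect exists, z scores depend on order, some sensitivity is lost, and the high-gain and low-gain cases are sorted partly by order. The consequence is negligible with no order effect, modest at 0.1 residual SD per visit and material from about 0.25 upwards. These sizes rest on an assumed linear effect and on one context per visit. Because the trial's own data can estimate the effect and the correction is cheap, the change is worth making before the analysis.

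**What to change.** In the Data analysis plan:

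1. Regress the differential on order (for example the lag k), with the order effect estimated separately in AD, svPPA and HC. Do not apply the HC slope alone to patients.
2. Subtract only the order component from each differential, leaving the group's context effect in place. Standardise on the order-adjusted HC mean, with the HC residual SD as the denominator.
3. Select cases on the adjusted score, show the unadjusted score beside it, report each selected case's order, and check that the high and low cases do not differ by order.
4. Do the same for observation, using its own lag from presence-only.
5. If allocation is still open, counterbalance orders within each of the three groups.

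Age, sex and education are optional covariates, to be added only if they relate to the differential in HC.

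The cost is one regression on data already held and a few degrees of freedom. The real limit is precision. With near-balanced orders the standard error of the slope is about 1/√(2n) residual SD: 0.10 for 46 HC, 0.13 for 30 AD and 0.18 for 16 svPPA. In svPPA the adjusted and unadjusted scores should therefore be read together.

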**Fig. 2 Fig2:**
[figure not shown]
Layout of experiment room in (**A**) presence-only condition, (**B**) observation condition, (**C**) collaboration condition, and (**D**) recall phase

During in the recall phase, only the participant and the experimenter will be present in the room. The participant will be seated at the same table as the experimenter.

#### Outcome of social memory task

For the learning phase, and for each social context, several scores will be collected: the number of trials performed before all the pairs of pictures are found, the number of clicks on each picture on the lefthand side of the screen, and on each picture in the grid. We will examine whether these scores are related to delayed recall performance, to establish whether a picture is remembered better and more accurately located if it has been seen several times.

For the picture recognition in the recall phase, we will record the numbers of correct responses (i.e., saying “yes” when the picture has previously been seen, and saying “no” when the picture has not been seen before) for each social context.

Finally, for the location recall, we will calculate an overall score for each social context. If a picture is correctly located in the grid, 1 point will be awarded, and if it is located in an adjacent box, 0.5 point will be awarded. If not, 0 point will be awarded.

We will assess whether social context influences the picture recognition and location recall scores, and use these scores to identify factors that could explain potential differences in recognition performance between social learning contexts.

#### Debriefing

To clarify the psychological mechanisms associated with performance in different social contexts, a debriefing phase will take place at the end of each learning session. Using Likert-type scales, participants will rate their confidence in the quality of the learning achieved, their pleasure and satisfaction during the task, their anxiety during the learning process, the effort put into learning, the attention paid to the task, and perceived task difficulty.

### Neuropsychological and clinical data

All the questionnaires and tests that will be used in this study are listed below. The scores they yield will allow us to identify determinants (social interactions, social abilities, cognitive skills, and personality traits) that could explain the potentially beneficial impact of the different social contexts on participants’ learning. These will then be used to define explanatory variables for differences in memory performance depending on social learning context.

#### Social interactions and social cognition

Three questionnaires will be used to identify the patients’ social interaction skills, in order to find out which social variables could explain differences in performance between the collaboration or observation context and the presence-only context. These questionnaires assess the quality of people’s social relationships [56], changes in socio-emotional [57] and exo-/egocentric behaviour since the onset of the disease, and social vulnerability [58].

Social cognition skills will be assessed with an empathy questionnaire [59, 60], and three tests developed in our research unit: a test of knowledge of social rules [61], a preference judgment test adapted from [62], and a social learning information test.

#### Memory abilities

This protocol will include several tests used in clinical neuropsychology to determine memory abilities. More specifically, we will assess visual episodic memory [63], working memory [64], and semantic memory [65, 66].

#### Personality traits

Personality traits will be assessed with the Temperament and Character Inventory developed by Cloninger [67]. This inventory is based on two fundamental components: temperament, which qualitatively describes the psychobiological dimensions of the individual’s personality; and character, which describes the individual’s levels of adaptation and maturity. The two subscales that are most relevant for the purposes of the study concern the character component. They are *Self-Directedness*, which corresponds to the level of individual maturity, and *Cooperativeness*, which reflects social maturity.

#### Additional assessment

Global cognitive impairment will be assessed using the MoCA [51]. Finally, executive functions in everyday life will be assessed with a questionnaire [68]. An MRI scan may be carried out to document patients’ brain lesions.

#### Demographic data

The relationship with the dyadic partner will be documented: nature of relationship (relative, friend, other), feeling of closeness, and number of years they have known each other. Some demographic information will also be collected: age, sex, highest degree obtained, living alone or not.

### MEM&SO study procedure

MEM&SO is a comparative cross-sectional study. Participants will be recruited from several centres (Caen, Rennes, Rouen, and memory clinics in Normandy). HC will be recruited in and around Caen, and the examinations of all participants will be performed in Caen. Registered on ClinicalTrials.gov (no. NCT05800028).

After the inclusion phase, the study will take place over 3 half-days, corresponding to the three study visits (see Fig. 3). Each visit will last 90 min, with a 10-minute break in the middle.

**Fig. 3 Fig3:**
[figure not shown]
Schedule for assessment visits. *The order of the three contexts will be randomly counterbalanced across the dyads

### Data analysis plan

Each participant’s performance in the presence-only context will serve as a reference score, and a differential score will be calculated by subtracting this reference score from the participant’s memory performance in the collaboration context. The *z* score of this differential score will then be calculated, based on the mean and standard deviation for the HC group. This will show whether each patient’s differential score differs significantly from that of the HC group. The same analyses will then be carried out for performance in the observation context.

As this study is designed to identify determinants (social interactions and abilities, cognitive skills, and personality traits) that could explain the differential scores for the collaboration and observation contexts, we will carry out multiple comparative case analyses [48–50], based on the differential scores for the collaboration context of at least three patients whose memory performance is substantially better in the collaboration condition, compared with the presence only condition, and for three patients whose performance is only minimally better. These six patients will be compared on their social skills (social interactions and abilities), personality (especially the cooperation and determination dimensions), and memory performance in classic neuropsychological tests. Following a logic of replication, other patients will be added to the analyses, to see whether a regular pattern emerges. The same analyses will be conducted on differential scores for the observation context.

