**Methods:**

Thirty dyads (patient with primary memory impairment who meets criteria for Alzheimer’s disease paired with caregiver), 16 dyads (patient meeting criteria for semantic variant of primary progressive aphasia paired with caregiver), and 46 dyads (healthy controls with no cognitive complaints) will be recruited. A nonverbal memory test (social memory task) will be administered to each dyad in three different social contexts (presence-only, observation, collaboration). Patients and healthy controls will also undergo a neuropsychological assessment to measure social (interactions and abilities), cognitive and personality aspects. Patients will be compared with controls on differential social scores calculated between the presence-only and collaboration contexts, and between the presence-only and observation contexts. A multiple comparative case study will be conducted to identify social, cognitive and personality variables that potentially explain the differential scores in the collaboration and observation contexts.

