
The main objective of the present study will be to assess whether social context (collaboration or observation) improves the memory performances of patients with a neurodegenerative disease who exhibit social cognition, memory or language disorders. A secondary objective will be to identify social (interactions and abilities), cognitive and personality variables that could explain differences in patients’ performances between collaborative and observation contexts.

To this end, a nonverbal memory test (social memory task) will for the first time be administered in three different social contexts (presence-only, observation, collaboration), to patients with AD, patients with svPPA, and healthy older people with no cognitive disorders. Participants will also undergo a neuropsychological assessment probing social (interactions and abilities), cognitive and personality aspects.

A multiple comparative case study will be conducted [48–50] to identify variables (social interactions and social abilities, cognitive skills, and personality traits) that could explain better performances in a collaboration or observation context than in a presence-only context.

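### The main objective is a gain within patients, but the only significance comparison in the data analysis plan is each patient's gain against the controls' gain

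*Protocol article*

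**What the plan says.** The main objective, at the end of the Background, is to "assess whether social context (collaboration or observation) improves the memory performances of patients with a neurodegenerative disease". The Discussion states the same purpose.

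Under Data analysis plan, presence-only performance is each participant's reference, and "a differential score will be calculated by subtracting this reference score from the participant’s memory performance in the collaboration context". A z score is then formed "based on the mean and standard deviation for the HC group". The plan says what this is for: to show whether each patient's "differential score differs significantly from that of the HC group". The observation context is handled in the same way. The Methods paragraph of the Abstract agrees: "Patients will be compared with controls on differential social scores calculated between the presence-only and collaboration contexts".

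Two other statements bear on the point. Under Outcome of social memory task: "We will assess whether social context influences the picture recognition and location recall scores", with no method, group or contrast named. Under Procedure for social memory task: "Each dyad will perform the task in all three contexts".

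**The concern.** The objective asks whether patients remember more after collaboration or observation than after presence-only. That is a mean difference within patients, to be compared with zero. The stated analysis compares the patient's difference with the controls' difference, which is a context-by-group interaction assessed one patient at a time. The two questions can have opposite answers.

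The case of equal gains is not remote. The Background reports that collaborative learning does better than learning alone both in older people with normal memory ageing and in patients with AD. If both groups benefit alike, the hypothesis is true and the z scores are centred on zero.

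The Discussion looks ahead to new rehabilitation techniques. That conclusion needs the gain within patients, and a comparison with controls does not supply it.

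**Working it through.** **Inputs from the protocol.** 30 AD, 16 svPPA and 46 HC dyads; 30 + 16 + 46 = 92 dyads, and 2 × 92 = 184 participants, as stated under Participants. Group sizes were set by feasibility. The article gives no SD, expected gain, alpha or power, so there is no power figure to reproduce.

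**Assumptions.** Differential scores are normal with the same SD in patients and controls. A patient is flagged when z > 1.96; the article gives no cut-off.

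**What z measures.** With patient differential D, HC mean m and HC standard deviation s, z = (D − m)/s. The expected numerator is (patients' mean gain − controls' mean gain). The patients' own gain enters only relative to the controls' gain.

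**Case 1: equal gains.** The expected numerator is 0, whatever the size of the gain. Then z/√(1 + 1/46) follows a t distribution with 45 df. The threshold becomes 1.96/1.011 = 1.939, and P(z > 1.96) = 0.029. Simulation with 20,000 runs gave 0.030. If that common gain is 1 SD, a paired test against zero in the patients has more than 99% power with n = 30 and 96% with n = 16.

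**Case 2: patients gain 0, controls lose 1 SD.** In simulation P(z > 1.96) = 0.18, and a two-sample comparison of AD with HC favours AD significantly in 99% of runs. The paired test in patients declares a gain in about 2.5% of runs, as it should.

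**Case 3: patients lose 0.5 SD, controls lose 1.5 SD.** P(z > 1.96) = 0.17, although the patients got worse.

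A significant z is therefore neither necessary (case 1) nor sufficient (cases 2 and 3) for improvement in patients.

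**Power of the contrast that the objective needs.** Two-sided 5% paired t-test, noncentrality = (gain/SD) × √n, before any adjustment for two contrasts:

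| Gain / SD of differential | AD, n = 30 | svPPA, n = 16 |
|---|---|---|
| 0.5 | 75% | 46% |
| 0.6 | 89% | 61% |
| 0.8 | 99% | 85% |

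At 80% power the detectable gain is 0.53 SD in AD and 0.75 SD in svPPA. These figures are illustrative only.

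**The case against.** **Context will be assessed, and this is a condensed article.** The outcome section does promise to assess the influence of social context, and a fuller document may name the test. This stands in part: it rules out saying that the trial ignores the within-patient question. It does not remove the mismatch. The article has a section that states which comparison is made and what it shows, and that comparison does not address the objective.

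**The case analysis reads scores within patients.** The plan also sorts patients by how much better they do than under presence-only. That is true, but the sorting is descriptive and serves to select cases.

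**The HC reference has a purpose.** This stands, and it shapes the fix. The section on the social memory task assigns 24 pictures to each context, so picture set and context cannot be separated. A patients-only test against zero would absorb any difference in difficulty between sets; the HC reference removes whatever part of that difference is common to both groups.

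**Stronger readings that a reader might infer.**

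- *The trial cannot answer its question.* It can: all three contexts are measured in everyone, and the differential is already computed.
- *A z near zero will be reported as no effect.* The plan does not say so.
- *The Background predicts that controls do worse in the observation context because they are observed.* There the participant watches the partner. The inhibition described in the Background concerns performing in front of others, which is closer to the presence-only reference, and facilitation is described as well. Case 2 is therefore a property of the statistic if controls lose ground for any reason, and not a forecast.
- *Controls will be at ceiling.* The article gives no data on this.

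**Conclusion.** The concern holds as a mismatch between the stated objective and the stated analysis. The only inferential step described tests whether a patient's gain is atypical of controls. On its own it can miss a benefit shared by both groups (about 3% of patients flagged, the chance level) or flag patients who did not gain (about 18% if controls lose 1 SD). These percentages rest on normal scores, equal SDs and a cut-off of 1.96, none of which the article gives.

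The design is sound for the question, and the correction is one of analysis wording. The power figures show only that a test within patients is feasible over a plausible range, with svPPA weak for gains near 0.5 SD.

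**What to change.** In the Data analysis plan, name as the main analysis the two within-patient contrasts, collaboration minus presence-only and observation minus presence-only, each tested against zero with Holm adjustment over the two. Report estimates with confidence intervals for AD and svPPA. One suitable model is a mixed model with context, group, context-by-group, order or visit, and a random participant effect. Keep the HC comparison and the z scores as a secondary analysis of whether a gain is atypical.

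Do not fit picture set together with context while each set belongs to one context. Either rotate the sets across contexts for dyads not yet tested and then adjust for set, or report the within-patient contrast beside the HC contrast and state that set difficulty is confounded with context.

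The cost is one more model and a few sentences. No further participants, visits or measurements are needed. Rotation means reassigning the picture sets in the task. Without it, the within-patient contrast carries any difference in set difficulty.
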